Previous studies have demonstrated the therapeutic effects of herbal medications in patients with UACS [13,14]. Wolbigachul-tang (WBGCT) is an herbal formula used to treat respiratory diseases such as asthma and allergic rhinitis [15,16]. It has been reported that WBGCT has antioxidant, anti-inflammatory, and antitussive effects on laryngeally-induced cough [17,18]. The hypothesized mechanism by which WBGCT has therapeutic effects against UACS-induced chronic cough is through the alleviation of upper airway inflammation. However, since the adverse effects of WBGCT including palpitation and insomnia have been reported [19], we will assess the safety of WBGCT, as well as its efficacy. In addition, to explore the possibility of using WBGCT with health insurance coverage, we will evaluate the economic feasibility of WBGCT by comparing it with Socheongryong-tang (SCRT), a health insurance-covered herbal formula used for respiratory symptoms. SCRT has been used for respiratory diseases, such as allergic rhinitis, asthma, and bronchitis [20,21], and has anti-inflammatory and anti-allergic effects that are promoted by inhibiting cytokine release, infiltration of inflammatory cells, and airway remodeling in animal models [22,23]. The safety of SCRT has been demonstrated in previous clinical trials and in vivo studies [24,25]. Considering its efficacy and safety, SCRT was selected as the investigational medicine in this study.

This study aims to investigate the efficacy, safety, and economic evaluation of WBGCT for UACS-induced chronic cough, a feasibility study to demonstrate its possibilities, including the duration of intervention, recruitment of participants, outcome measures, and effect size before this trial.

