### 2.5. Safety Assessment

For the safety assessment, adverse events (AEs), vital signs, electrocardiograms, and clinical laboratory tests (complete blood count, liver function test, and urine analysis) will be assessed. AEs are harmful and unintended signs, symptoms, and diseases in patients taking investigational drugs, which do not necessarily imply a causal relationship with the investigational drugs. Vital signs and AEs will be assessed at every visit after the investigational medications are administered (visits 2, 3, and 4). The investigators will record the date of onset, severity, results of AEs, action taken against investigational medications, causal relationship between AEs and investigational medications, other suspected medicines, and treatments for AEs. When AEs occur, the principal investigator should conduct continuous follow-up until they disappear, or the patients are in a stable condition. All serious AEs will be reported to the principal investigator within 24 h.

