Descriptive statistics for each group regarding demographic characteristics and baseline data will be presented. Continuous variables will be expressed as means and confidence intervals, and an independent *t*-test or Wilcoxon rank-sum test will be performed depending on their normality. Categorical variables are expressed as frequencies and percentages, and χ2 test or Fisher’s exact test will be conducted. The primary outcome measures will be analyzed using the mixed effect model repeated measure (MMRM), setting each group and visit as a fixed effect and participants as a random effect. If necessary, the fixed effects will include variables with significant differences in demographic characteristics or variables that can affect chronic cough. Analysis of the primary outcome measures are expressed as mean and 95% confidence interval (CI). Among the secondary outcome measures, CSS scores for 4 weeks against baseline and cough VAS, NDS, LCQ-K, and QCSCS scores will be analyzed using the same methods as the primary outcome measure. Depending on normality, Student’s paired *t*-test or Wilcoxon signed-rank test will be used to analyze differences in scores before and after treatment. The IMOS and IMPSS scores at 2- and 4-week intervals will be analyzed using Fisher’s exact test. Repeated-measures analysis of variance (RM ANOVA) will be used to compare the differences in the changes in CSS score trends between the groups, and Dunnett’s procedure for multiple comparison correction will be used. When performing the Student’s paired *t*-test, Wilcoxon signed-rank test, or RM ANOVA, a missing data will be substituted with Last Observation Carried Forward (LOCF) or Multiple Imputation (MI).

A safety evaluation will be conducted on participants who receive Interventions at least once. The number of AEs between the groups will be compared using Fisher’s exact test. Differences in laboratory test variables before and after treatment will be analyzed using the Student’s paired *t*-test or Wilcoxon signed-rank test.

Economic evaluations will be performed from both social and limited social perspectives. In sensitivity analysis, the available variables will be analyzed using a one-way sensitivity analysis with a tornado diagram. If necessary, a probabilistic sensitivity analysis will be conducted using the distribution and representative values of the variables.

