**Figure 2 healthcare-11-02733-f002:**
[figure not shown]
The potential mechanisms of ingredients in WBGCT for UACS-induced chronic cough. Previous studies demonstrated that the ingredients had anti-inflammatory, antioxidative, anti-allergic, antibacterial, and antiviral effects, affecting airway smooth muscle and lung tissue [43,44,45,46,47,48,49,50,51]. UACS; upper airway cough syndrome, WBGCT; Wolbigachul-tang.

**Table 1 healthcare-11-02733-t001:** Schedule of enrollment, interventions and outcome measurements.

	Study Period			
	Enrollment	Allocation	Post- Allocation	Follow-Up
Visit	1	2	3	4
Timepoint	−2 Weeks	0	Week 2 ± 4 Days	Week 4 ± 4 Days
Enrollment				
Informed consent	X			
Eligibility screen	X			
Allocation		X		
Demographic characteristics	X			
Social and economic characteristics	X			
Medical history	X			
Chest X-ray, EKG	X			
Vital signs	X	X	X	X
Pulmonary Function Test	X			
Paranasal Sinuses X-ray	X			
Interventions				
WBGCT				
SCRT				
Assessments				
Clinical laboratory test ^1^	X		X	
Pregnancy Diagnosis Test	X			
CSS	X	X	X	X
Cough VAS		X	X	X
NDS		X	X	X
Cough and sputum severity standard		X	X	X
LCQ-K		X	X	X
IMOS & IMPSS			X	X
EQ-5D-5L		X	X	X
PICCQ	X			
Adverse reaction assessment		X	X	X
Compliance test		X	X	

^1^ CBC (erythrocyte count, leukocyte count, differential count, hemoglobin, hematocrit, platelet count, and erythrocyte sedimentation rate); LFT (AST, ALT, γ-GTP, ALP, BUN, creatinine, total bilirubin, and glucose); and U/A (urine chemical test paper, and urine microscopy). Abbreviations. ALP, alkaline phosphatase; ALT, alanine aminotransferase; AST, aspartate aminotransferase; BUN, blood urea nitrogen; CBC, complete blood count; CSS, cough symptom score; EQ-5D-5L, 5-level EuroQol 5-dimensional questionnaire; γ-GTP, gamma-glutamyl transpeptidase; IMOS, integrative medicine outcome scale; IMPSS, integrative medicine patient satisfaction scale; LCQ-K, Leicester cough questionnaire-Korean version; LFT, liver function test; NDS, nasal discharge score; PICCQ, pattern identification for chronic cough questionnaire; SCRT, Socheongryong-tang; U/A, urine analysis; VAS, visual analog scale; WBGCT, Wolbigachul-tang.

**Table 2 healthcare-11-02733-t002:** Composition of Wolbigachul-tang and Socheongryong-tang.

Latin Name	Amount (g)
Wolbigachul-tang	
Ephedrae Herba	3.75
Zizyphi Fructus	0.67
Gypsum Fibrosum	1.25
Atractylodis Rhizoma	2.50
Glycyrrhizae Radix et Rhizoma	1.25
Zingiberis Rhizoma Recens	0.83
Socheongryong-tang	
Ephedrae Herba	0.30

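### The adverse-event comparison applies Fisher's exact test to numbers of events rather than to participants with an event, and the electrocardiogram listed for safety is scheduled only before allocation.

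*Protocol article*

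**What the plan says.** **AE comparison.** Section 2.9 (Statistical Analysis) bases safety on everyone dosed: "A safety evaluation will be conducted on participants who receive Interventions at least once". It then assigns Fisher's exact test to AEs in these terms: "The number of AEs between the groups will be compared using" that test. Section 2.5 (Safety Assessment) defines the thing counted at event level, "AEs are harmful and unintended signs, symptoms, and diseases in patients taking investigational drugs", and collects it repeatedly: "Vital signs and AEs will be assessed at every visit after the investigational medications are administered (visits 2, 3, and 4"). Nowhere does the article define the comparison as the number of participants with at least one AE.

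**Electrocardiogram.** Section 2.5 opens with "For the safety assessment, adverse events (AEs), vital signs, electrocardiograms, and clinical laboratory tests". In Table 1 the row "Chest X-ray, EKG" has one mark, at Visit 1 (two weeks before time 0). Allocation is at Visit 2. The Introduction links the safety objective to a reported cardiac symptom: "since the adverse effects of WBGCT including palpitation and insomnia have been reported".

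**The concern.** Fisher's exact test needs independent units, each falling in exactly one cell of a two-by-two table. Participants classified as having an AE or not meet that requirement. Events do not. A participant with headache, insomnia and palpitation supplies three events that share one cause and one person. Once an arm has more events than participants, no table with a participant denominator can be formed at all. With about 15 per arm, one or two participants with many complaints could create an apparent difference between the products.

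The second issue is a mismatch between text and schedule. A measure recorded only before allocation cannot show what happens on treatment. A reader of section 2.5 would expect the trial to say something about electrocardiograms under the two products, and the printed schedule yields no such data.

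**Working it through.** **Inputs from the article.** Section 2.2.2 gives 12 per group and 20% dropout. Check: 12 / (1 − 0.20) = 15 per group, 30 in total, which matches the stated figure. The article gives no AE rate, no number of AEs per participant and no significance level for safety. Those used below are assumptions.

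**Illustration 1 (hypothetical).** Two of 15 participants in one arm have 10 AEs between them. Two of 15 in the other arm have one each.
- Events as units: table [10, 5; 2, 13]. With 12 events in total, the two-sided p sums the hypergeometric terms at least as extreme: 2 × [C(15,10)·C(15,2) + C(15,11)·C(15,1) + C(15,12)·C(15,0)] / C(30,12) = 2 × (315,315 + 20,475 + 455) / 86,493,225 = 672,490 / 86,493,225 = 0.0078.
- Participants as units: table [2, 13; 2, 13], p = 1.0.

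**Illustration 2 (hypothetical).** Two participants in one arm have six AEs between them, and the other arm has none.
- Events: [6, 9; 0, 15], p = 2 × C(15,6) / C(30,6) = 2 × 5,005 / 593,775 = 0.017.
- Participants: [2, 13; 0, 15], p = 2 × C(15,2) / C(30,2) = 2 × 105 / 435 = 0.48.

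**False-positive rate under no group difference.** Simulation with 20,000 runs per scenario, 15 per arm and a two-sided 0.05 level. The assumed share of participants with any AE is 20%, 30% or 50%. Each affected participant has 1 + Poisson AEs, with mean 1, 2 or 3.

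| Unit given to Fisher's test | Mean 1 AE per affected participant | Mean 2–3 AEs |
|---|---|---|
| Participants with any AE, of 15 | 1.6–1.8% | 1.6–1.8% |
| Events, of 15 (runs where a table exists) | 1.6–1.8% | about 14–30% |
| Events, of 15 × 14 = 210 person-days | 0.2–0.6% | about 9–23% |

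With a mean of 2–3 AEs, an arm has more than 15 events, so that no table exists, in 2–97% of runs. If every affected participant has exactly one AE, event and participant counts coincide and the test is valid. The fault lies entirely in multiple events per person.

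**Electrocardiogram.** No arithmetic applies. Rows of Table 1 side by side:

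| Measure | Visits marked | Mark after allocation visit? |
|---|---|---|
| Vital signs | 1, 2, 3, 4 | Yes |
| Clinical laboratory tests | 1, 3 | Yes |
| Electrocardiogram | 1 | No |

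Section 2.5 lists all three as safety measures. Only the electrocardiogram has no later record.

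**The case against.** **The AE wording may be shorthand.** The preceding sentence takes participants as the safety population, and section 2.9 elsewhere uses the χ² or Fisher's exact test for categorical variables in the usual participant-level way. On that reading the planned test is valid. This stands as a possibility, and it limits the point to the test as literally written. It does not remove the point, because the article has fixed both the test and the quantity and does not name the participant as the unit. This is a stated choice, not detail left to an analysis plan.

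**The examples are invented.** True. No AE rate is given, and the article never says it will divide events by participants. The figures show how far the two units can diverge, not what this trial will find.

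**The electrocardiogram may be meant for screening.** Section 2.5 states no post-dose visit for it, section 2.9 plans no analysis of it, and Table 1 places it beside the chest X-ray among enrolment items. So no planned analysis fails. Palpitation can still be recorded as an AE. What remains is the disagreement between the section 2.5 list and Table 1.

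**Stronger readings that the document does not support.**
- A reader might infer that the whole safety evaluation fails. Vital signs and laboratory tests are scheduled after allocation and are untouched.
- A reader might infer that events before dosing will be counted, since Table 1 places Visit 2 at time 0. Section 2.5 largely answers this: it defines AEs in patients taking the study drugs and describes the assessments as following administration.
- A reader might treat the before-after laboratory tests as an error because no between-arm test is named. Silence on a between-arm test is not a mistake; adding one would be an optional improvement.
- A reader might add that 15 per arm says little about uncommon AEs. That is a matter of sample size in an openly exploratory trial, and changing the unit of analysis would not alter it.

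**Conclusion.** The point holds in two limited parts.

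1. Taken literally, the AE comparison uses non-independent units and is invalid whenever participants have more than one event. Under the assumed AE patterns, the false-positive rate of the event-level test is several times the 5% level, against 1.6–1.8% at participant level. That size rests wholly on the assumed rates; the structural fault does not. If participants with an AE were meant, the test is right and the sentence is wrong.

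2. Section 2.5 and Table 1 disagree on the electrocardiogram as a safety measure. As printed, no on-treatment electrocardiogram information can arise. That matters because the article itself gives palpitation as a reason to assess safety.

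Both are worth correcting before analysis. Neither undermines the rest of the safety plan.

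**What to change.** In section 2.9, replace the AE sentence so that it compares, by arm, the number of participants with at least one AE starting after the first dose, using Fisher's exact test with an exact confidence interval for the risk difference. State that total event counts are reported descriptively. Naming onset after the first dose also removes any doubt left by the Visit 2 label.

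Reconcile section 2.5 with Table 1 on the electrocardiogram. If the schedule stands as printed, describe it as a screening measure and state that no conclusion about electrocardiogram change on treatment will be drawn.

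Optionally, add a between-arm comparison of laboratory change adjusted for baseline.

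The cost is one or two sentences of analysis wording and one reconciliation. The AE change needs no extra data or participants.

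### Laboratory safety values get only a paired before-after test, so WBGCT and SCRT are never compared on them

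*Protocol article*

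**What the plan says.** The safety paragraph of section 2.9 covers everyone who took the intervention: "A safety evaluation will be conducted on participants who receive Interventions at least once". It then names two analyses with different contrasts.

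- Adverse events: "The number of AEs between the groups will be compared using Fisher’s exact test". This is a comparison of the arms.
- Laboratory variables: "Differences in laboratory test variables before and after treatment will be analyzed using the" Student's paired t-test or the Wilcoxon signed-rank test. This is a comparison over time. The text does not say whether it is run within each arm or on both arms together.

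In Table 1 the row "Clinical laboratory test" is marked at visit 1 (screening) and visit 3 (week 2), so before and after can only mean those two visits.

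A between-group test for continuous data does appear earlier in section 2.9: "Continuous variables will be expressed as means and confidence intervals, and an independent" t-test or rank-sum test. That sentence directly follows the one on demographic and baseline data and does not mention laboratory variables.

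Section 2.5 also bears on the point. It defines adverse events broadly ("AEs are harmful and unintended signs, symptoms, and diseases in patients taking investigational drugs") and has them documented per participant: "The investigators will record the date of onset, severity, results of AEs, action taken against investigational medications", among other items.

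**The concern.** Section 2.1 describes a randomised, double-blind, parallel trial with an active comparator and names safety among its purposes. Randomisation protects only a comparison between arms. A before-after change within an arm, or across both arms, mixes any product effect with whatever else changes between screening and week 2.

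This is a stated choice of test, so it is not a detail left to a fuller document. If the plan is followed, the laboratory results will be a set of paired p-values. If these are produced by arm, the natural way to learn anything about WBGCT against SCRT is to see which arm has significant changes. That is not a test of the difference, and it goes wrong often at this sample size.

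**Working it through.** **The plan's own figure.** Section 2.2.2 takes 12 per group and allows for 20% dropout: 12 / (1 − 0.20) = 15 per group, 30 in total. This reproduces. The article gives no figure for the laboratory analysis. The checks below therefore use 12 and 15 per arm from the plan, and a two-sided 0.05 level, which is an assumption because none is stated for laboratory tests.

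**1. Do paired tests within each arm stand in for a comparison?** Suppose both arms have the same true mean change, in units of the SD of change. The assumed range is 0 to 0.8 SD. If each arm's paired t-test is significant with probability p, the chance that exactly one of the two is significant is 2p(1 − p). Simulation (40,000 trials per row) gave:

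| Per arm | Equal shift (SD) | p, one arm | One significant, one not | Two-sample test of change positive |
|---|---|---|---|---|
| 12 | 0 | 0.051 | 9.5% | 5.0% |
| 12 | 0.3 | 0.159 | 26.9% | 4.9% |
| 12 | 0.6 | 0.479 | 50.2% | 4.9% |
| 12 | 0.8 | 0.716 | 40.7% | 5.0% |
| 15 | 0 | 0.051 | 9.6% | 5.0% |
| 15 | 0.3 | 0.189 | 30.8% | 4.8% |
| 15 | 0.6 | 0.573 | 48.9% | 4.9% |
| 15 | 0.8 | 0.819 | 29.5% | 5.0% |

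The formula agrees: for example, 2 × 0.479 × 0.521 = 0.499. With no difference between the products, the two tests disagree in about 27% to 50% of trials when there is a common shift and about 10% when there is none. The between-arm test stays near 5% throughout.

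**2. What would a between-arm estimate deliver?** The 95% CI half-width for the difference in mean change is t × √(2/n) SD.

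- 12 per arm: 2.074 × √(2/12) = 0.85 SD.
- 15 per arm: 2.048 × √(2/15) = 0.75 SD.

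Simulated power for a true 1.0 SD difference is 65% (12 per arm) and 75% (15 per arm). For 0.5 SD it is 22% and 26%. These figures are for unadjusted change; the baseline-adjusted version was not simulated.

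**3. How does a paired test react to one large rise?** Take one participant with a rise R and no change in the other n − 1. The mean is R/n, the SD is R/√n and the standard error is R/n, so t = 1 however large R is. With assumed noise of SD 8 U/L in all participants:

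| Per arm | Rise (U/L) | Shift in arm mean (U/L) | Paired t significant | Signed-rank significant |
|---|---|---|---|---|
| 12 | 40 | 3.3 | 2.1% | 4.7% |
| 12 | 80 | 6.7 | 0.1% | 4.8% |
| 12 | 160 | 13.3 | 0.0% | 4.4% |
| 15 | 40 | 2.7 | 2.7% | 4.4% |
| 15 | 80 | 5.3 | 0.2% | 5.3% |
| 15 | 160 | 10.7 | 0.0% | 4.7% |

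The signed-rank column rests on 3,000 trials per row. Neither test responds to a single large rise. A between-arm difference in means dilutes it in the same way, so this calls for counts, not for another test of means. Counts at this size are descriptive too: Fisher's exact test needs 5 against 0 to fall below 0.05 (p = 0.037 with 12 per arm, 0.042 with 15).

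**The case against.** The best defence is that before-after change answers a question the between-arm difference cannot. There is no placebo arm, as the Discussion acknowledges, and both products contain Ephedrae Herba and Glycyrrhizae Radix et Rhizoma (sections 2.3.1 and 2.3.2). A change common to both would cancel in a comparison of arms. This stands, and it is why before-after change should be kept, though as a description.

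A reader might infer from the third check that the safety plan conceals individual toxicity. The documents do not support that. Adverse events include harmful signs, are recorded per participant with severity and causality, and are compared between groups. A marked laboratory change can surface there, although the article does not say that abnormal values are logged as adverse events. The insensitivity belongs to the paired test alone. Shift tables and abnormality counts are commonly left to the full protocol or SAP, so their absence here is not a fault.

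Two further arguments should not be pressed. Counting about 15 quantitative tests in two arms gives 1 − 0.95^30 = 79% for at least one false positive, but this assumes independence among plainly related tests; 15 between-arm tests would still give 1 − 0.95^15 = 54%. Regression to the mean from the screening limits is possible, but those limits cut only far-out values on a few of the tests, and the size of the effect is not established.

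Finally, no passage says that an arm difference will be inferred from paired p-values. That is true, but it leaves the laboratory data with no comparison at all.

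**Conclusion.** The point holds in a limited form. For laboratory values the plan specifies only a paired test, and so never makes the comparison for which the trial was randomised. The sentence on independent-samples tests does not repair this, because it stands with the baseline data and a different test is named for laboratory variables.

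The 27% to 50% disagreement rests on a 0.05 level, normally distributed changes, an assumed common shift of 0.3 to 0.8 SD, and tests run by arm. With no shift it is about 10%. If the test is pooled there is no disagreement to observe, but also no information on the arms.

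For an exploratory trial of 30 this is a worthwhile and nearly free improvement, not a threat to its main result. Adverse events already have a between-group test, and a between-arm laboratory analysis would give wide intervals.

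**What to change.** In section 2.9, replace the laboratory sentence with three elements:

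1. **Main analysis.** For each quantitative variable, the between-arm difference at visit 3 adjusted for the visit 1 value, with a 95% CI. State that it is read as an estimate, because power is low at 12 to 15 per arm.
2. **Descriptive summary.** Mean or median change by arm with a CI and without a significance test, to show changes common to both products.
3. **Useful addition.** By arm, the number of participants at or above twice the upper normal limit for ALT, AST, ALP and creatinine at visit 3. This borrows the limit already used in exclusion criterion 9, purely as a reporting threshold.

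The cost is a few sentences and two standard tables. The visit 1 and visit 3 samples are already scheduled, so no new data are needed. The change should be made before unblinding.

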## 2. Methods

### 2.1. Study Design

This is a randomized, double-blind, active-comparator-controlled, parallel, exploratory clinical trial to evaluate the efficacy, safety, and economic feasibility of WBGCT for UACS-induced chronic cough. Thirty participants will be recruited for this trial and randomly assigned to the WBGCT and control groups in a 1:1 allocation ratio. This trial consists of screening, 2-week treatment, and 2-week observation periods. The medications will be administered three times a day for 2 weeks. The detailed study design is summarized in Figure 1 and Table 1.

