
#### 2.2.2. Sample Size

With reference to an exploratory pilot study in which a sample size of 12 per group was recommended [26], the sample size of this trial was 24 participants (12 per group). This is the first randomized controlled trial to investigate the efficacy, safety, and economic evaluation of WBGCT for UACS-induced chronic cough [18]. Considering a 20% dropout rate, 30 participants (15 per group) will be recruited.

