### 2.6. Economic Evaluation

The primary economic endpoint is the incremental cost-utility ratio (ICUR) calculated at every visit using the EQ-5D-5L. The secondary economic endpoint is the incremental cost-effectiveness ratio (ICER) calculated at every visit using the variables for clinical effectiveness. A cost evaluation will be performed using micro-costing based on data, including survey results, medical records, and administration data, while gross costing will be conducted as needed. Cost assessments will be performed using surveys conducted on visits 2, 3, and 4. For participants who dropped out of the trial early, the costs until the investigational medication ended will be collected.

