## 5. Conclusions

This study aims to demonstrate the effects of WBGCT on UACS-induced chronic cough. As WBGCT has been used widely for respiratory diseases over a long period of time with few side effects, WBGCT is expected to be a safe and effective agent for UACS-induced chronic cough. Moreover, considering that our intervention is Korean medicine, we used pattern identification to obtain additional information on whether certain patterns of patients respond better than others to the treatment. Additionally, we perform an economic evaluation of WBGCT compared to SCRT, expecting the expansion of newly applied health insurance-covered herbal formulas. Our study will support the efficacy, safety, and economic feasibility of WBGCT and provide evidence for its clinical use.

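### The only committed uncertainty analysis for the primary economic endpoint is a one-way tornado; the analysis that could carry joint sampling error is optional, with no trigger stated

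*Protocol article*

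**What the plan says.** Section 2.6 (Economic Evaluation) of the protocol article states: "The primary economic endpoint is the incremental cost-utility ratio (ICUR"), with utilities from the EQ-5D-5L. A cost-effectiveness ratio is secondary.

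Section 2.9 (Statistical Analysis) names two analyses of economic uncertainty and ranks them.

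- Unconditional: "In sensitivity analysis, the available variables will be analyzed using a one-way sensitivity analysis with a tornado diagram".
- Conditional: "If necessary, a probabilistic sensitivity analysis will be conducted using the distribution and representative values of the variables". The article does not say what would make it necessary.

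Section 2.2.2 takes its size from a rule of thumb: "With reference to an exploratory pilot study in which a sample size of 12 per group was recommended". It then inflates for dropout: "Considering a 20% dropout rate, 30 participants (15 per group) will be recruited".

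Section 5 states the expected result: "Our study will support the efficacy, safety, and economic feasibility of WBGCT and provide evidence for its clinical use". The same section ties the economic evaluation to wider insurance coverage of herbal formulas, while section 4 calls the trial small and preliminary.

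**The concern.** The ICUR is a ratio of two between-arm differences, each estimated here from 24 to 30 people over 4 weeks. Its main uncertainty is the sampling error in participants' costs and utilities, which may be correlated within a person. A tornado diagram shows how the result responds when one input is moved and the rest are held fixed. It suits assumptions such as unit costs, but it gives no joint interval for incremental cost and incremental QALY.

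The article is not silent on method. It makes the tornado mandatory and the probabilistic analysis discretionary. For data of this size that ranking is the wrong way round, and with no trigger the decision can follow sight of the ICUR.

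A ratio is also a weak summary on its own. A negative ICUR arises both when WBGCT is cheaper and better and when it is dearer and worse. What is at stake is one of the trial's three aims, which is meant to inform insurance coverage: a favourable-looking ratio could be reported with no statement of how imprecise it is.

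**Working it through.** The check takes a single, fully costed 4-week ICUR, so it does not depend on when the ratio is computed or how dropouts are costed.

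**1. The plan's own figure.** 24 / (1 − 0.20) = 30, and 12 / 0.80 = 15 per arm. The stated sample size reproduces. The article gives no precision figure for the economic endpoint, so there is nothing further to reproduce.

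**2. Standard error of the QALY difference.** From the article: EQ-5D-5L at weeks 0, 2 and 4 (Table 1), and n = 12 or 15 per arm. Assumed: the same utility SD *s* at each visit, 0.08 to 0.15; correlation 0.6 between any two visits; QALY as the trapezoid area, unadjusted for baseline. The horizon is T = 28/365.25 = 0.0767 years.

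- The trapezoid weights are 1/4, 1/2, 1/4.
- Variance factor = (1/16 + 1/4 + 1/16) + 2 × 0.6 × (1/8 + 1/16 + 1/8) = 0.375 + 0.375 = 0.75.
- SE = T × *s* × √0.75 × √(2/n).
- Smallest (*s* = 0.08, n = 15): 0.0767 × 0.08 × 0.866 × 0.365 = 0.0019.
- Largest (*s* = 0.15, n = 12): 0.0767 × 0.15 × 0.866 × 0.408 = 0.0041.

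A simulation of 40,000 trials per setting gave the same ends of the range.

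**3. What a utility gain is worth.** The gain of 0.03 is illustrative.

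- Present from day 0: 0.03 × 28/365.25 = 0.0023 QALY, which is 0.0023/0.0041 = 0.6 to 0.0023/0.0019 = 1.2 SE.
- Baselines equal, gain present at weeks 2 and 4: the trapezoid counts 3/4 × 28 = 21 days, so 0.03 × 21/365.25 = 0.0017 QALY, which is 0.4 to 0.9 SE.

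**4. Sign of the utility difference at one visit.** P(correct sign) = Φ(0.03 / (SD × √(2/n))).

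| SD (assumed) | n = 12 | n = 15 | n = 100 |
|---|---|---|---|
| 0.10 | 0.77 | 0.79 | 0.98 |
| 0.20 | 0.64 | 0.66 | 0.86 |

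With 12 to 15 per arm, a real difference of 0.03 therefore shows the wrong sign in about 21% to 36% of trials.

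**5. Sign of the ratio with no true difference in cost or QALY.** For correlation ρ between the two estimated differences, P(ICUR < 0) = 1/2 − asin(ρ)/π.

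- ρ = 0: 0.50, of which 0.25 dominant and 0.25 dominated.
- ρ = −0.3: 0.60, of which 0.30 and 0.30.
- ρ = +0.3: 0.40, of which 0.20 and 0.20.

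Simulation gave the same at n = 12, 15 and 100 per arm. With skewed (lognormal) costs and ρ = 0 it gave 0.496 (n = 12) and 0.501 (n = 15).

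**6. What happens if costs do differ.** Suppose QALYs are equal but WBGCT is dearer by *k* cost SDs, and let *r* be willingness-to-pay × QALY SD / cost SD. Then P(net benefit > 0) = Φ(−*k* / (√(2/n) × √(1 + *r*²))). At n = 12, *k* = 0.5 with *r* = 0.5 gives 0.14, and *k* = 0.25 with *r* = 2 gives 0.39. With *k* = 0 it is 0.50 at any n.

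**The case against.** A reader might infer that the economic conclusion will be read off the point ICUR, and that 12 to 15 per arm makes it a coin toss. The documents do not support that. They state no decision rule, willingness-to-pay or net-benefit criterion. The 50% chance of a favourable point estimate follows from assuming no true difference, and it is the same at 100 per arm. It also needs equal costs, which nothing in the article establishes: SCRT is the insurance-covered product and WBGCT is a candidate for coverage. Step 6 shows the figure moving well away from 50% when costs differ. Small numbers do matter, but through the imprecision in steps 2 to 4.

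Other objections have force.

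- The probabilistic analysis as described does use distributions as well as representative values, so it could carry joint uncertainty. The criticism is that it is optional, not that it is the wrong tool.
- Intervals, a cost-effectiveness plane, a threshold and a trigger may stand in the full protocol or analysis plan, which is not shown. An ICUR cannot be computed without incremental cost and incremental utility, and nothing says these will be withheld. So the sign ambiguity belongs to a bare ratio and is not shown to be how this trial will report.
- A tornado whose ranges were confidence limits would show some sampling error, though still one input at a time.
- The trial calls itself exploratory, and the wording in section 5 covers efficacy and safety too.

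These limit the point but do not remove it. The article ranks the two analyses explicitly and makes the less suitable one the only commitment.

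**Conclusion.** The point holds as one about the choice and ranking of methods, and it is worth correcting because the remedy is cheap. As written, an analysis of sampling error for the primary economic endpoint is discretionary and can be decided after the result is known. The error it would describe is large: a sustained utility gain of 0.03 amounts to about 0.6 to 1.2 SE of the 4-week QALY difference, or 0.4 to 0.9 SE if it appears only from week 2.

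These sizes rest on the assumed utility SD (0.08 to 0.15) and between-visit correlation (0.6), which the article does not give. The range of 40% to 60% for a negative ratio rests on no true difference in either cost or QALY and a correlation between +0.3 and −0.3. It is a property of ratios at any sample size, not a forecast for this trial.

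**What to change.** In section 2.9:

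- Replace the conditional probabilistic analysis with a committed non-parametric bootstrap that resamples participants within arm and keeps each person's cost and utility together.
- Report the 4-week incremental cost and incremental QALY, each with a 95% CI, and the incremental net monetary benefit with an interval over a stated range of willingness-to-pay.
- Give the ICUR only with its quadrant.
- Keep the tornado for unit-cost assumptions.

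In section 5, say that the study *will give preliminary estimates of* economic feasibility instead of saying that it will support it.

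The cost is a little more analysis on data already collected, with no added burden on participants. Bootstrap intervals from 12 to 15 people per arm with skewed costs tend to be somewhat too narrow and should be described as approximate. The main downside for the sponsor is that the economic result will probably be stated as inconclusive.
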